## Methods

### Study design

A three-arm cluster randomised controlled trial with a theory-based process evaluation will be undertaken. Hospitals (clusters) will be randomised to the multicomponent implementation strategy delivered with high or low external remote facilitation or a no facilitation control group receiving only usual care (inactive control group).

This protocol complies with the Standard Protocol Items: Recommendations for Interventional Trials (SPIRIT) [33], CONSORT extension for cluster randomised trials [34] and Template for Intervention Description and Replication (TIDiER) [35] checklists (Additional files 1, 2 and 3).

### Study setting

Australian and New Zealand public and private hospitals with a stroke unit or stroke service.

### Eligibility and recruitment of participants

#### Hospitals

To be eligible to participate in the study, hospitals must:Have a pre-existing stroke unit (organised care within a specific ward in a hospital by a multidisciplinary team who specialise in stroke management) [36] or a stroke service (no dedicated stroke unit but with integrated hospital stroke services based on agreed hospital service delineations) [3];Have at least one staff member to fulfil the role of hospital clinical champion;Nominate staff to undertake patient medical record audits pre- and post-implementation and enter data into the Australian Stroke Data Tool or New Zealand Stroke Register; andGrant permission to the researchers to obtain patient 90-180 day follow-up data from the Australian Stroke Clinical Registry (AuSCR) and the New Zealand Stroke Register for the economic evaluation (for those hospitals contributing data to these Registries).

In Australia, eligible hospitals will be systematically recruited through invitations to all stroke units/stroke services known to the Stroke Foundation. The study will also be advertised through the AuSCR, Stroke Foundation, Australian Stroke Nurses Education Network and state-based stroke clinical networks via email, newsletters and websites. In New Zealand, recruitment will occur through the National Stroke Network, Stroke Nurse Forum Aotearoa and clinical networks. A short recruitment video will also be developed and shared to these organisations in advertisement emails and via social media.

#### Patients

The medical records of eligible patients will be audited by participating hospital staff. Patients will be eligible if they are aged 18 years or older and have a diagnosis of ischaemic stroke, intracerebral haemorrhage, or stroke of undetermined origin with the following International Classification of Diseases, Tenth Revision (ICD-10) codes: I61.0 - I61.9 (intracerebral haemorrhage), I63.0 - I63.9 (cerebral infarction), I64 (stroke not specified as haemorrhagic or infarction) and I62.9 (intracranial haemorrhage unspecified) [37]. Patients will be excluded if they are admitted for palliative care.

### Randomisation and blinding

The unit of randomisation will be hospitals. Hospitals will be randomised in blocks of five to one of the three study arms—high- or low-intensity external remote facilitation or a no facilitation control group—in a 2 (high intensity):2 (low intensity):1 (no facilitation) ratio. Prior to randomisation, hospitals will be stratified by country, participation in a stroke registry and remoteness area factor (metropolitan/major cities or regional/rural as per the Accessibility and Remoteness Index of Australia [ARIA+] [38] and urban or non-urban as per the New Zealand REGIONS Care project [39] classification). Hospitals that meet the inclusion criteria will be enrolled on a rolling basis until the target sample size is reached. A flow diagram outlining the randomisation and intervention allocation is shown in Fig. 1.

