### Control group

Hospitals randomised to the control group will only have access to the publicly available FeSS Protocols. No active intervention/external remote facilitation will be provided by the researchers, and these hospitals will perform usual stroke care practices and collect data on the FeSS processes of care. Control group hospitals will not receive the detailed FeSS audit and feedback reports that will be provided to intervention group hospitals. However, there may be some hospitals randomised to the control group that participate in the biennial national stroke acute care audits and/or contribute continuous data on the FeSS elements to the AuSCR. As per standard practice, these hospitals will routinely receive basic audit and feedback reports from the Stroke Foundation and/or AuSCR as part of quality improvement initiatives undertaken external to the trial. If the research team receive any proactive emails from control group hospitals regarding the study (excluding questions about data collection), these hospitals will be directed to the Quality in Acute Stroke Care webpage hosted on the Australian Catholic University website (https://www.acu.edu.au/qasc). If the questions relate to the national stroke audit or AuSCR data entry or platform issues, they will be referred to the national stroke audit coordinator or AuSCR, as required. At study completion, clinical champions from control group hospitals will receive access to the online FeSS education package after providing their post-implementation data.

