### Sample size calculation

We used Monte Carlo simulation to estimate the detectable difference-in-difference between any two treatment arms with 80% power at a 5% significance level. Previous QASC Trial and QASC Europe studies suggest we could expect an ICC of 0.075, cluster level correlation between baseline and post-test of 0.3 and baseline defect-free care of 10%. With an assumed 60 hospitals with 60 patients included per hospital pre- and again 60 patients included post-intervention (i.e. *n*=120 patients per hospital and using an unequal randomisation ratio of 2 (high intensity):2 (low intensity):1 (no facilitation intensity), we calculated that a test between two 24 hospital arms would be able to detect a difference-in-difference of 1.5 (odds ratio (OR)) and a test between one 12 hospital arm and one 24 hospital arm would be able to detect a difference-in-difference of 2 (OR).

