### Data analysis

#### Primary and secondary outcomes

The unit of analysis is at the patient level. Analysis will be by intention-to-treat. Demographic and clinical characteristics of patients (e.g. treatment in a stroke unit, discharge destination, ability to walk on discharge, duration of hospital stay, discharge modified Rankin Scale score) will be summarised using descriptive statistics and presented by group allocation. Analysis for overall adherence with all monitoring and treatment elements of the FeSS Protocols and adherence to each of the monitoring and treatment elements for Fever, Sugar and Swallowing will be undertaken based on the following comparisons: low-intensity facilitation versus control groups, high-intensity facilitation versus control groups and low-intensity facilitation versus high-intensity facilitation groups. Analysis will include comparison of outcomes between metropolitan and rural/remote hospitals; difference in proportions of change in monitoring and treatment for fever, hyperglycaemia and swallowing between stroke units versus stroke services. Analysis of outcomes will use logistic regression with adjustment for rurality, stroke unit presence; presence of Angels consultants; baseline thrombolysis rate (<11% vs ≥11%; 11% is the average annual rate based on the 2021 Stroke Foundation clinical audit) [5]; age, sex, stroke severity and correlation of outcomes within hospitals. Effect sizes will be estimated for each intervention group relative to the control as well as for comparisons between the low-intensity facilitation and high-intensity facilitation intervention groups. No interim analyses are planned.

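### Two of the three randomisation strata, country and stroke-registry participation, are missing from the stated outcome model; the likely cost is slightly conservative standard errors, not bias

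*Protocol article*

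**What the plan says.** In the protocol article, under Randomisation and blinding, "The unit of randomisation will be hospitals" and "hospitals will be stratified by country, participation in a stroke registry and remoteness area factor". Remoteness is metropolitan or regional/rural in Australia, and urban or non-urban in New Zealand. Allocation is 2:2:1: "Hospitals will be randomised in blocks of five to one of the three study arms". Enrolment is rolling.

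Under Data analysis (Primary and secondary outcomes), the covariates are listed one by one: "Analysis of outcomes will use logistic regression with adjustment for rurality, stroke unit presence; presence of Angels consultants; baseline thrombolysis rate" (with a cut-off at 11%), then "age, sex, stroke severity and correlation of outcomes within hospitals". Country and registry participation are not in that list or anywhere else in the analysis text.

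Under Control group, some control hospitals may take part in the national audits or contribute to the Australian registry, and "these hospitals will routinely receive basic audit and feedback reports from the Stroke Foundation and/or AuSCR".

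**The concern.** A stratified randomisation balances the arms on the stratifying factors. If these predict the outcome, the treatment contrast varies less from one allocation to the next than under simple randomisation. A model without the factors does not see this: it leaves their variance between hospitals and reports a standard error that is too large. The test becomes conservative and part of what the stratification was meant to gain is lost. A model without the factors also cannot correct imbalance that arises when blocks are not filled.

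The article gives some reason to think that the two factors could matter. All 36 stroke services in New South Wales had the protocols rolled out in 2014, whereas New Zealand has had no systematic implementation (Background). Registry hospitals receive routine feedback (Control group). The arm comparisons rest on only 24 v 24 or 12 v 24 hospitals, so avoidable loss of precision is worth a line in the plan.

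The analysis plan is not shown and may add the strata. The point stands because the article does not leave the covariates open: it gives an explicit list that departs from its own strata.

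**Working it through.** **1. Strata against covariates**

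| Factor | Stratified | In model |
|---|---|---|
| Remoteness / rurality | yes | yes |
| Country | yes | no |
| Registry participation | yes | no |
| Stroke unit, Angels consultants, thrombolysis rate | no | yes |
| Age, sex, stroke severity | no | yes |

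**2. Inputs from Sample size calculation.** ICC 0.075, pre-post cluster correlation 0.3, baseline defect-free care 10%, 60 hospitals, 60 patients per hospital per period, "with 80% power at a 5% significance level" (two-sided assumed). Not in the documents, and assumed: the share f of between-hospital variance explained by country and registry participation, taken as 0 to 30%, and the ICC read on the latent logistic scale.

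**3. The plan's own figure.** The article states detectable odds ratios of 1.5 (24 v 24) and 2 (12 v 24). From the inputs above I get 1.97 and 2.31 for a difference-in-difference, and 1.68 and 1.89 with adjustment for baseline. These do not reproduce 1.5, but the simulation code and ICC scale are not shown, and the present point does not depend on them.

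**4. Variance per hospital, log-odds scale**
- Between hospitals: (0.075/0.925) × π²/3 = 0.267.
- Sampling, one period at 10%: 1/(60 × 0.1 × 0.9) = 0.185.

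**5. Post-period comparison, 24 v 24, null case.** SE = √[2 × (0.267(1 − f) + 0.185)/24].
- f = 0: √(2 × 0.452/24) = 0.194.
- f = 10%: √(2 × 0.425/24) = 0.188.
- f = 30%: √(2 × 0.372/24) = 0.176.

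**6. Difference-in-difference, 24 v 24, null case.** Stable stratum effects subtract out, so f does not enter when they are the stable part: SE = √[2 × (2 × 0.267 × 0.7 + 2 × 0.185)/24] = √(2 × 0.744/24) = 0.249.

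**7. Simulation.** Hospital log-odds, stratified blocks of five, high v low arm, 3,000 runs per setting. Assumed prevalences: country 20/80, registry 60/40, regional 40/60. The model contains rurality alone, or rurality plus country and registry. Power is at odds ratio 1.5.

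| Contrast, f | Strata omitted | Strata included |
|---|---|---|
| Post-period, 0% | no difference | no difference |
| Post-period, 10% | power 52% | power 54% |
| Post-period, 30% | SE 0.193 v true SD 0.180; type I error 3.5%; power 53% | SE 0.176 v true SD 0.178; type I error 5.3%; power 60.5% |
| Difference-in-difference, 30%, stable | SE 0.249; type I error 5.2%; power 36.5% | SE 0.250; type I error 5.3%; power 36.4% |

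Monte Carlo error for a power near 50% is √(0.25/3000), or 0.9 points.

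**8. How plausible is 30%?** With equal variance in both periods, a pre-post correlation of 0.3 means that all stable hospital factors together account for 0.3 × 0.267 = 0.080. Stable effects of country and registry at f = 30% would use all of it. The 30% rows are therefore a ceiling for stable effects.

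**9. Unfilled blocks.** If blocks run within strata, 2 × 2 × 2 gives up to eight strata, each with at most four hospitals in an unfilled last block: 8 × 4 = 32. As 60 is a multiple of five, the total must be too, so at most 30 of 60 hospitals. With six strata (registry nested in country) the limit is 20. These are bounds, not forecasts.

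**The case against.** A reader might infer a larger gain. With an assumed post-period rate of 20%, the variance per hospital is 0.267 + 1/(60 × 0.2 × 0.8) = 0.371, and removing 10 to 30% of 0.267 lowers it by 7 to 22%. The documents do not support that as the size of the problem. The trial is sized on a difference-in-difference, and the Discussion describes the aim as comparing pre-post changes, where stable stratum effects cancel. The 20% rate appears nowhere; odds ratio 1.5 from a 10% baseline gives about 14% (odds 1.5/9 = 0.167). The upper end meets the ceiling in step 8. Moreover, the model already holds rurality, stroke unit presence, Angels consultants and thrombolysis rate, which may overlap with country and registry, so only the additional share counts.

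The evidence that the strata are prognostic is also thin. Routine reports go to hospitals in the national audits, the registry or both, so feedback does not cleanly separate registry from other hospitals. The Discussion expects the effect of these reports to be minimal because the feedback is passive. Nothing in the article compares adherence by registry status, or by country on a common measure. Registry participation may be nested in country, since New Zealand hospitals enter data directly into their national registry.

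All of this limits the size. It does not remove the mismatch, which is plain in the text. The analysis section also names no pre-post or arm-by-period term, so a post-period comparison cannot be excluded, and different prior exposure to the protocols could affect change as well as level.

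**Conclusion.** The point holds as a minor one. Two of three stratification factors are absent from an explicit covariate list, without a reason. If they are prognostic, the standard errors are somewhat too large and imbalance from unfilled blocks is not corrected.

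The size is unknown from the documents. It is about zero for a difference-in-difference with time-invariant stratum effects, and about 2 power points for a post-period comparison if the two factors explain 10% of between-hospital variance. It is larger only if they explain more or also predict change. These figures rest on the latent-scale ICC, the assumed share and the assumed prevalences.

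A reader might take the mismatch to mean that the primary result would be biased or its type I error inflated. Neither follows: even in the 30% post-period case the error rate with the strata omitted was 3.5%, below nominal.

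**What to change.** Add country and registry participation to rurality as fixed effects in all primary and secondary models, each as classified at randomisation. If registry participation turns out to be nested in country, use one combined stratum factor. Where change from baseline is modelled, also let these factors vary by period: main effects alone do little for a difference-in-difference, and the period terms are what recover precision if the strata predict change. If the factors are to stay out, give the reason.

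The cost is one line in the analysis plan and about two hospital-level degrees of freedom, a few more with the period terms. No new data are needed, since both factors must be known at randomisation.

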**Fig. 1 Fig1:**
[figure not shown]
CONSORT flow diagram

Computer-generated randomisation of the hospitals will be performed independently by a statistician blinded to group allocation and not otherwise involved in the study ensuring allocation concealment. Staff at participating hospitals will be blinded to the intensity (high, low or none) of external remote facilitation provided.

### Intervention

The QASC Australasia intervention is a multicomponent implementation strategy aimed at changing clinician and team behaviour [26, 27]. Multidisciplinary stroke unit/stroke service staff will be required to work together to achieve the study outcomes. The intervention components, mapped to several Theoretical Frameworks (Additional file 4), are outlined below and summarised in Table 1.

**Table 1 Tab1:** Components of QASC Australia Intervention

Components	Intervention groups		Control group
	High-intensity facilitation	Low-intensity facilitation	No facilitation
FeSS Protocols	✓	✓	✓
Online FeSS education package	✓	✓	X
Evidence-based audit and feedback report	✓	✓	X
External remote facilitation:			
*Videoconference sessions for timeline, action plan development and implementation*	✓	X	X
*Reminders*	Project process, intervention and data collection reminders	Project process, intervention and data collection reminders	Project process and data collection reminders only
*Email and telephone support*	Proactive and reactive	Reactive	X

#### FeSS protocols

The evidence-based care bundle of FeSS Protocols (Table 2) refined from our previous FeSS implementation studies [1, 2] will be used in this national translational study.

**Table 2 Tab2:** Summarised elements of the Fever, Hyperglycaemia (Sugar) Swallow (FeSS) Protocols

**Fever (*****n*****=2)** • Temperature readings monitored and recorded at least four times per day for the first 72 h • If temperature => 37.5°C treat with paracetamol or other anti-pyretic **Sugar (Hyperglycaemia) (*****n*****=3)** • Formal venous glucose on admission to Emergency Department or stroke service • Blood glucose level readings monitored and recorded at least four times per day for the first 48 h, to continue for 72 h if BGL unstable • If blood glucose level >10 mmol/L (180mg/dl) treat with insulin **Swallowing (*****n*****=2)** • Swallow screen or swallow assessment within 4 h of admission and prior to being given oral food, drink, or medications • Referral to speech pathologist for full assessment for those who fail the swallow screen	

#### Implementation strategy

All intervention components (FeSS Protocols, online FeSS education package, FeSS audit and feedback report) including external remote facilitation will be provided online. Participating hospitals will nominate at least one clinician (nurse where possible, or if not, then a speech pathologist) currently working in the stroke unit/stroke service to act as a hospital clinical champion. Preferably, this would be a senior clinician(s) with stroke expertise, but more importantly, someone recognised as a stroke clinical leader within their hospital, ready to implement change at the hospital and encourage use of the FeSS Protocols by their local team. Evidence suggests that key attributes of a clinical champion which have the potential to improve implementation outcomes are influence, ownership, physical presence at the point of change, grit, persuasiveness and participative leadership style [40]. Our team has had considerable success in NSW and in Europe working with clinical champions to support evidence translation locally [1, 3, 18]. The evidence-based implementation strategy comprises an educational package [41], audit and feedback reports [42], local clinical champions [43], barrier and enabler assessments [44, 45], action plans [25], reminders [46] and external remote facilitation [12] (Table 1).

#### Online FeSS education package

Education and training of stroke clinicians is important in ensuring the delivery of evidence-based stroke care and improvement in outcomes for patients with stroke [47]. The use of information and communication technologies in the education of clinicians is now common globally. E-learning environments integrate information, in the form of text and multimedia, and can be designed for self-directed learning or learning in real time [48]. This delivery method for learning has gained popularity due to the potential benefits of increasing the accessibility of information to remote learners, lower costs, personalised instruction in terms of content and pace of learning and facilitating frequent content updates [49].

The online FeSS education package consists of three components: An Online Education Resource Package; a Train-the-Trainer Education Package; and a Clinician Education Package. All components of the package will be provided to clinical champions in intervention hospitals. Each component is outlined in Table 3 and described further below:

**Table 3 Tab3:** Components of the FeSS education package

**Online Education Resource Package** • Videos with the following topics: o FeSS is one of the most cost-effective interventions in acute stroke care o A fever is not the smoke, it’s the fire. Put it out ASAP o Blood sugar is the fuel on the fire: keep it regulated o A sip of water can be deadly after strokes: Check their swallowing first o Leading change can be hard. Here’s how to make it easier o Why do an audit? o How to do an audit • Downloadable hard-copy resources o FeSS Protocols o PowerPoint slides for multidisciplinary meeting o PowerPoint slides for education session o Action plan template o PowerPoint slides for ASSIST education o PowerPoint slides for ASSIST competency assessment o QASC Australia data dictionary o QASC Australia data collection user manual o Flowchart of project milestones o Frequently asked questions (FAQ) document	
**Train-the-Trainer Education Package** (relevant to study group allocation) • High- and low-intensity external remote facilitation groups o All components of the online education resource package • Control group will receive only downloadable hard-copy resources o FeSS Protocols o PowerPoint slides for ASSIST education o PowerPoint slides for ASSIST competency assessment o QASC Australia data dictionary o QASC Australia data collection user manual o Frequently asked questions (FAQ) document	
**Clinician Education Package** (high- and low-intensity external remote facilitation groups only) • Short (5-7 minute) videos with the following topics: o FeSS is one of the most cost-effective interventions in acute stroke care o A fever is not the smoke, it's the fire. Put it out ASAP o Blood sugar is the fuel on the fire: keep it regulated o A sip of water can be deadly after strokes: Check their swallowing first o Why do an audit? o How to do an audit • Downloadable hard-copy resources o FeSS Protocols	

##### Online Education Resource Package

An online education resource package comprising a suite of seven videos of 5–7-min duration and downloadable hard-copy resources will be developed by the research team in collaboration with educational psychologists specialised in adult learning research from the School of Psychology, University of Queensland. Video topics will be based on case studies using stroke experts, consumers, role-playing actors and animations. Learning activities will be included at the end of each video with summative case studies to assess participants knowledge following completion of the videos. The package will be hosted on the Australian Catholic University OpenLearning webpage. The design of the videos will incorporate implementation science behaviour change techniques which will be mapped to behaviour change frameworks and taxonomy (v1), COM-B and TDF [27, 50, 51] (Additional file 5) to provide clinicians with the capability, opportunity and motivation to implement the FeSS Protocols. In addition, the online video package will be designed using effective multimedia principles to optimise learning in viewers by leveraging the two key information processing systems—sight and sound, and managing cognitive load [52, 53]. Designs were informed by adult learning principles previously developed and evaluated by members of our team who developed and implemented a suite of educational resources. These resourcses successfully changed behaviour in primary school teachers to increase physical activity in children [54–57].

